# Study background and scientific rationale

## Background information

### Overview of rectal cancer

Colorectal cancer is one of the most common malignant tumors of the digestive tract worldwide. According to the 2020 Beijing Cancer Registry Annual Report, the incidence rate of colorectal cancer among Beijing's registered residents ranked second among men and fourth among women in 2017. Regardless of gender, the mortality rate of colorectal cancer ranked second among malignant tumors. Among them, rectal cancer accounts for approximately 50% of all colorectal cancers and is a key research object in clinical diagnosis and treatment. However, the early clinical manifestations of rectal cancer are not typical. Most patients seek medical attention due to symptoms such as anemia, changes in stool consistency, abdominal pain, and abdominal masses, at which point the tumor has often progressed to an advanced stage. Currently, radical surgery is the main treatment method for rectal cancer in clinical practice. However, for locally advanced patients, it is difficult to completely remove the lesion through surgery alone, and recurrence is common after surgery. Therefore, it is necessary to explore individualized comprehensive treatment strategies for locally advanced rectal cancer patients to improve their prognosis.

### Treatment strategies for rectal cancer

At present, clinical treatment guidelines for rectal cancer both domestically and internationally recommend preoperative radiotherapy and chemotherapy for patients with locally advanced middle and low rectal cancer (clinical stage ≥T3N+). Numerous studies have shown that the local recurrence rate of locally advanced rectal cancer significantly decreases after preoperative radiotherapy. In clinical research, Rodel et al classified the degree of pathological response after rectal cancer radiotherapy into three grades: complete pathological response, partial pathological response, and poor pathological response. The results showed that in patients with rectal cancer who received preoperative radiotherapy and radical surgical resection, the 5-year disease-free survival rate (DFS) was 86% for the complete pathological response group, 75% for the partial pathological response group, and 63% for the poor pathological response group (P = 0.006). Fokas et al also obtained similar results: in 386 patients who received rectal cancer radiotherapy and chemotherapy, the 10-year cumulative DFS of the complete pathological response group, partial pathological response group, and poor pathological response group were 89.5%, 73.6%, and 63% respectively, with statistical significance (P = 0.008). These studies indicate that the degree of tumor regression after preoperative radiotherapy for rectal cancer significantly affects the prognosis of patients. Therefore, for patients with rectal cancer, how to further improve the degree of pathological response after radiotherapy is a key issue for improving the prognosis of rectal cancer.

The research found that patients with higher infiltration density of CD4+ and CD8+ T lymphocytes in tumor tissues before radiotherapy for rectal cancer had a better response to radiotherapy for rectal cancer. Anitei et al further analyzed the enrichment score of T lymphocytes in tumor tissues of rectal cancer patients before radiotherapy, and the results showed that patients without a response to radiotherapy had a lower immune score, and the study found that the mutation load in tumor tissues before radiotherapy was positively correlated with the sensitivity to neoadjuvant therapy, and patients with higher mutation load had higher sensitivity to radiotherapy and chemoradiotherapy, while the characteristics of tumor mutation load and neoantigens could be indirectly reflected through the tumor immune microenvironment. The research team earlier also found through bulk sequencing analysis that the activation of related immune pathways was widely enriched in different radiotherapy-sensitive samples of rectal cancer.

The characteristics of the tumor microenvironment of rectal cancer patients may be correlated with the efficacy of radiotherapy, and in radiotherapy-resistant tumor tissues, abnormal tumor blood vessels, more myeloid-derived suppressive cells (MDSCs) and tumor-associated macrophages (TAMs) infiltration, the latter inhibit the proliferation of dendritic cells by secreting cytokines, leading to the downregulation of co-stimulation and activation of Tregs cells to suppress the enrichment of cytotoxic T lymphocytes. Therefore, for patients with rectal cancer undergoing radiotherapy, the target for relieving immune suppression may be a key entry point for further improving the efficacy of radiotherapy and improving prognosis.

A study reported at ASCO in 2019 showed that the pCR rate of MSS-type locally advanced rectal cancer patients treated with preoperative long-course concurrent radiotherapy combined with nivolumab (PD-1 inhibitor) reached 30%, and the pCR rate of MSI-H patients reached 60%. A study at the ASCO conference in 2021 reported that 27 cases of rectal cancer received preoperative radiochemotherapy combined with immunotherapy, and the overall pCR rate was as high as 48%, the downstaging rate reached 70%, and the rate of preservation of anus reached 89%. These studies suggest that preoperative radiotherapy combined with immune checkpoint inhibitors can effectively improve the efficacy of rectal cancer radiotherapy and has important clinical application prospects. However, it is still unclear which rectal cancer patients can benefit from radiotherapy combined with immune checkpoint inhibitor treatment, and the biomarkers for treatment benefit and new targets have not yet been clarified, and further research is needed.

# Study Endpoints

## Primary Endpoints

Pathologic complete response rate (pCR) based on TRG scoring criteria: refers to the percentage of subjects with no viable tumor cells (including lymph nodes, stage ypT0N0M0) seen under light microscopy.

## Secondary Endpoints

- Sphincter preserving rate：proportion of patients with preserved anal sphincter

Time Frame: instantly after surgery;

- Immune-related adverse event rate: adverse event rate that is deemed to be associated with PD-1 inhibition

Time Frame: from commencing of PD-1 inhibition to the 30th day after surgery;

- Treatment-related adverse event rate: adverse event rate that is deemed to be associated with all treatments

Time Frame: from commencing of treatment to the 30th day after surgery;

- Incidence rate of surgical complications: incidence rate of surgical complications within 30 days after surgery

Time Frame: within 30 days after surgery;

Exploratory Endpoints

- Longitudinal single-cell RNA-seq (scRNA-seq) and single-cell TCR-seq (scTCR-seq) of tumor tissue and matched peripheral blood to identify immune programs of response vs resistance

# Research design

## Overall Design

This study is a single-arm, open-label, phase II trial to observe and evaluate the efficacy and safety of capecitabine-based long-term radiotherapy followed by 3 cycles Sintilimab (PD-1 inhibitor) for locally advanced rectal cancer.

The study aims at the treatment-naïve patients with gastric or gastroesophageal junction adenocarcinoma at the staging of cT3-4 or N+, M0 (staging according to AJCC version 8).

With pathological complete response rate (pCR) as the primary study endpoint, 46 patients with resectable locally advanced gastric adenocarcinoma and gastroesophageal junction adenocarcinoma who have not received treatment are planned to be enrolled.

Subjects are enrolled after signing informed consent and passing screening.

Subjects will receive the following treatments:

45-50.4Gy/25 fractions + 5-FU long-course radiotherapy and chemotherapy (5 times per week for 5 weeks, total dose of 45 to 50.4Gy) before surgery →PD-1 monoclonal antibody (Sintilimab, 200mg, once a week, for 3 weeks) →radical surgery

The surgery was scheduled 8-12 weeks after radiotherapy completion.

Radiographic assessment:

All lesions are recorded and assessed according to RECIST 1.1. Imaging examinations include chest CT, enhanced CT scans of the abdomen and pelvis, and chest CT plain scan + abdominal and pelvic MRI scans could be performed if allergic to enhanced CT contrast agents; brain enhanced MRI or enhanced CT is also required to rule out brain metastases in patients with suspected brain metastases. Bone scan should be performed when bone metastasis is confirmed or clinically suspected. Colonoscopy examinations should be conducted before the start of radiotherapy, after the completion of radiotherapy, and after immunotherapy to evaluate the therapeutic effects.

Within 1 weeks after the radiotherapy; within 1 weeks after the frist dose of PD-1 monoclonal antibody in Cycle 3; at the end of treatment; and imaging assessments at least every 3 months in subsequent Year 1 and at least every 6 months from Year 2 until radiographic progression or recurrence, receipt of other antineoplastic therapy, withdrawal of informed consent, loss to follow-up, or death.

If treatment is discontinued during the treatment period for reasons other than radiographic progression, imaging should be performed at the end of treatment unless imaging has already been performed within 28 days.

Pathological assessment: According to the operation guidelines specified in the protocol, pathological efficacy, degree of eradication, ypT staging and ypN staging are evaluated.

Subjects will be followed for survival every 3 months in the first year and every 6 months from the second year after the end of treatment, and their survival status and subsequent anti-tumor treatment will be collected and recorded until death or loss to follow-up.

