# Protocol Summary

| **Study Title** | Neoadjuvant Long-course Chemoradiotherapy Followed by Immunotherapy for Locally Advanced Mid-low Rectal Cancer (NLCCRIT-LARC) |
| --- | --- |
| **Protocol No.** | NCT06493240 |
| **Version No** | 1.0 |
| **Sponsor** | Peking University People’s Hospital |
| **Principal Investigator** | [name] |
| **Participating sites** |  |
| **Research design** | A single-arm, open-label, phase II trial |
| **Study objective** | **Primary Objective**   - pathological complete response (pCR) rate   **Secondary Objectives**   - Sphincter preserving rate - Immune-related adverse event rate - Treatment-related adverse event rate - Incidence rate of surgical complications   **Exploratory Objectives**   - Longitudinal single-cell RNA-seq (scRNA-seq) and single-cell TCR-seq (scTCR-seq) of tumor tissue and matched peripheral blood to identify immune programs of response vs resistance |
| **Research subjects** | Previously untreated and confirmed by biopsy as rectal adenocarcinoma and MRI shows no distant metastasis, stage II/III (except T4b) |
| **Treatment Regimen** | The treatment regimen is 45-50.4Gy/25 fractions + 5-FU long-course radiotherapy and chemotherapy (5 times per week for 5 weeks, total dose of 45 to 50.4Gy). On the 15th day after the end of radiotherapy and chemotherapy, tumor tissue was biopsied and PD-1 monoclonal antibody (Sintilimab, 200mg, once a week, for 3 weeks) treatment was performed. The surgery was scheduled 8-12 weeks after radiotherapy completion. |

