### Dosing Regimen

Sintilimab monotherapy after radiotherapy (3 cycles)

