**The specific dose and mode of administration are as follows:**

Sintilimab: 200 mg, every 3 weeks, with 21 days as a cycle. This product is for intravenous injection only. Intravenous infusion over 30 minutes. The infusion tube used in the infusion must be equipped with a sterile, pyrogen-free, low-protein-binding infusion tube filter (pore size 0.2-1.2 μm). This product should not be administered by intravenous bolus or single rapid intravenous injection. This product can be directly infused with 10mg/ml solution, or diluted with sodium chloride solution for injection (9mg/ml, 0.9%) or glucose solution for injection (50mg/ml, 5%), the concentration can be as low as 1mg/ml.

The study drug is administered until the protocol-specified treatment termination criteria occur.

Imaging assessment is performed for the subjects within 1 weeks of the last dose of Sintilimab therapy; surgery is performed for operable subjects 2 weeks after the last dose.

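### The Protocol Summary and Overall Design order sintilimab weekly for three weeks, while the dosing section orders it every three weeks for three cycles

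*Protocol*

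**What the plan says.** Two schedules for sintilimab stand in the current text.

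- **Weekly.** The Treatment Regimen row of the Protocol Summary says "PD-1 monoclonal antibody (Sintilimab, 200mg, once a week, for 3 weeks) treatment was performed". Overall Design repeats the schedule in its treatment line, introduced by "Subjects will receive the following treatments": "Sintilimab, 200mg, once a week, for 3 weeks".
- **Every three weeks.** The Dosing Regimen section, under the specific dose and mode of administration, says "Sintilimab: 200 mg, every 3 weeks, with 21 days as a cycle", and sets three cycles.

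The section on the treatment period and end of treatment refers the reader to 5.1.2 for study medication. By the order of headings, 5.1.2 is the Dosing Regimen section. The Dose Adjustments section sets a minimum of 12 days between sintilimab doses.

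Surgery is also timed in two ways. Overall Design and the Summary say "The surgery was scheduled 8-12 weeks after radiotherapy completion". The dosing section says "surgery is performed for operable subjects 2 weeks after the last dose".

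**The concern.** The dose interval of the investigational drug has to be fixed in the protocol itself; a statistical analysis plan cannot supply it. As written, the Summary and Overall Design tell a site to dose every 7 days and the dosing section tells it to dose every 21 days.

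Two things are at stake. The first is safety: a site that follows the front of the protocol gives the PD-1 inhibitor at three times the rate in the dosing section. The second is interpretation. With a single arm, the regimen given is the whole basis for reading the pCR rate and the immune-related adverse event rate. If the schedule is ambiguous, so is the treatment to which those results belong.

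**Working it through.** No sample-size, power or error-rate figure is involved, so there is no stated figure to reproduce. The check compares the two schedules and then tests each against the protocol's other timing rules.

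**Inputs**
- Dose: 200 mg in both texts.
- Interval: 7 days (Protocol Summary, Overall Design) or 21 days (Dosing Regimen).
- Number of doses: three. This is the plain reading of the weekly text, and one per cycle in the dosing section.
- Start: day 15 after chemoradiotherapy, from the Summary ("On the 15th day after the end of radiotherapy and chemotherapy, tumor tissue was biopsied", with sintilimab in the same sentence).
- Minimum interval: 12 days (Dose Adjustments).
- Surgery: 8-12 weeks after radiotherapy, that is 8 × 7 = day 56 to 12 × 7 = day 84; and 14 days after the last dose.

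**Formulas.** Rate = dose / interval in weeks. Dose days = 15 + interval × (0, 1, 2). Surgery day under the 2-week rule = last dose + 14.

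| | Weekly text | 3-weekly text |
|---|---|---|
| Rate | 200 / 1 = 200 mg per week | 200 / 3 = 66.7 mg per week |
| Total | 3 × 200 = 600 mg | 3 × 200 = 600 mg |
| First to last dose | 2 × 7 = 14 days | 2 × 21 = 42 days |
| Dose days | 15, 22, 29 | 15, 36, 57 |
| Against the 12-day minimum | 12 − 7 = 5 days short | met |

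The ratio of rates is 200 / 66.7 = 3.

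**Fit with the surgery rules.** On the 3-weekly schedule, surgery two weeks after the last dose falls on 57 + 14 = day 71, or 71 / 7 = 10.1 weeks, inside days 56-84. The dosing section and the surgery window therefore agree. On the weekly schedule, the window in Overall Design can also be kept: surgery would fall 56 − 29 = 27 to 84 − 29 = 55 days after the last dose. That breaks nothing in Overall Design, but it does not match the 2-week rule of the dosing section.

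**Early stopping, a smaller gap.** The dose-modification text allows sintilimab to be stopped permanently. On the 3-weekly schedule the 2-week rule then gives:
- after dose 1: 15 + 14 = day 29, which is 56 − 29 = 27 days before the window opens;
- after dose 2: 36 + 14 = day 50, which is 56 − 50 = 6 days before it opens.

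The protocol does not say which rule prevails.

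**The case against.** The best reply is that a careful reader would not be misled. Overall Design itself speaks of three cycles and schedules imaging in Cycle 3. A cycle is defined as 21 days in the dosing section, and the treatment-period section names that section as the place for detail. The weekly phrase then looks like a slip for once every three weeks. This lowers the chance of misdosing but does not remove it. The weekly wording appears twice and can be carried out as it stands, and no rule says which section prevails. The start day appears only in the Summary, in the same sentence as the weekly schedule, so a site has to read that sentence to know when to begin.

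It is also fair to say that intent is inferred. The protocol never declares which schedule was meant, and both Overall Design and the sections near the dosing text carry remnants of another protocol (gastric cancer, nivolumab). The 12-day minimum stands among dose-modification principles written for combination treatment, so it is supporting evidence only. For this reason the correction should be confirmed clinically first. The documents give no toxicity data by schedule, so the harm is a potential one whose size cannot be stated.

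On surgery timing, the withdrawal section lists patients who cannot complete the plan as possible withdrawals, which may cover some who stop early. It sets no surgery date, however. That part of the point is minor.

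**Conclusion.** The contradiction is real and should be corrected. The Protocol Summary and Overall Design call for three times the dosing rate of the dosing section (200 against 66.7 mg per week), with the same 600 mg total given over 14 rather than 42 days. The 3-weekly schedule is the well-supported reading, because of the pointer to the dosing section, the three-cycle wording and the fit to the surgery window.

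The calendar rests on a first dose on day 15 and an undelayed course. The conclusion that the two schedules conflict rests on neither. Nothing in the document shows that any patient was dosed weekly, and no harm from early surgery is claimed. The unranked surgery rules are a secondary gap that arises only when doses are delayed or stopped early.

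**What to change.** 1. In the Treatment Regimen row of the Protocol Summary and in the treatment line of Overall Design, replace the weekly schedule with 200 mg every 3 weeks for 3 cycles, once the clinical team has confirmed that this is the regimen.
2. Add one sentence stating which surgery limit prevails, two weeks after the last dose or 8-12 weeks after radiotherapy, when doses are delayed or sintilimab is stopped early. Surgery should not be made conditional on receiving the third dose.
3. If any patient was in fact dosed weekly, disclose it and describe pCR and safety by schedule received, without a formal comparison.

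The cost is a protocol amendment with ethics approval: two text corrections and one added sentence. Sample size and the primary analysis do not change.

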# Subject selection and withdrawal

Subjects must meet the following criteria to be allowed to participate in this study. All medical or non-medical conditions of each subject are taken into account for their compliance or non-compliance with the trial criteria.

Before a subject is enrolled in the study, the investigator should review, confirm and document whether the subject is suitable for the study.

## Inclusion Criteria

Patients must meet all of the following inclusion criteria to be enrolled in the study:

1. Patients voluntarily participate in the study and sign the informed consent form;
2. Age ≥ 18 years and ≤ 80 years;
3. Previously untreated and confirmed by biopsy as rectal adenocarcinoma;
4. MRI shows no distant metastasis, stage II/III (except T4b)
5. The lower edge of the tumor must be within 10 cm of the anal margin;
6. Willing and able to comply with the research protocol;
7. Agree to use blood and tissue samples for research;
8. No history of anti-tumor treatment (such as radiotherapy, chemotherapy, immunotherapy, biology, herbal medicine, etc.);
9. ECOG score 0-2;
10. No immune system diseases (such as systemic lupus erythematosus, rheumatoid arthritis, systemic vasculitis, scleroderma, pemphigus, dermatomyositis, mixed connective tissue disease, autoimmune hemolytic anemia, hyperthyroidism/hypothyroidism, ulcerative colitis, autoimmune hemolytic anemia, HIV infection, etc.);
11. No significant functional impairment of major organs (such as heart, lungs, liver, kidneys, etc.);
12. No jaundice or gastrointestinal obstruction; No acute/chronic infection;
13. No obvious abnormalities in blood routine and biochemical tests: neutrophils≥1.5×109/L, hemoglobin≥80g/L, platelets≥100×109/L, total bilirubin≤1.5×ULN, ALT, AST≤2.5×ULN;
14. No social or mental disorders;
15. For women of childbearing age, the serological pregnancy test result needs to be negative, and effective contraception measures need to be taken within 60 days;

## Exclusion criteria

Patients with any of the following are not to be enrolled in the study:

1. Patients with multiple types of cancer, or accompanied by tumors other than rectal cancer;
2. Having received any anti-cancer treatment (surgery, medication, etc.) within the past 5 years;
3. Recent history of major surgery;
4. Conditions affecting the absorption of capecitabine through the gastrointestinal tract (such as inability to swallow, nausea, vomiting, chronic diarrhea, etc.);
5. Having any type of uncontrolled, severe, accompanying disease, allergic to any component of the study; estimated survival period ≤ 5 years due to any reason;
6. Preparing or previously having undergone organ or bone marrow transplantation;
7. Receiving immunosuppressive or systemic hormone therapy within 1 month before inclusion for immunosuppression;
8. For patients with a history of central nervous system diseases, the investigator needs to judge whether the clinical severity hinders signing the informed consent or affects the patient's oral medication compliance;
9. Other situations/problems that may affect the research results or lead to the termination of the study (such as alcohol abuse, drug abuse, etc.);
10. Pregnant or lactating women, or women planning to conceive during treatment;

## Subject withdrawal of study treatment

Subjects can withdraw from the trial at any time on their own, or are withdrawn by the investigator due to safety or behavioral reasons, or because they are unable to comply with protocol-required study visit times or procedures at their site.

Reasons for withdrawal of a subject from the study may include:

1. Patients for whom combined organ resection is necessary during the operation;
2. Patients with distant metastasis confirmed during the operation, including liver, pelvic cavity, ovaries, peritoneum, and distant lymph node metastasis;
3. Patients who require emergency surgical resection due to intestinal obstruction, intestinal perforation, intestinal bleeding, etc;
4. Patients who request to withdraw from the study cohort for various reasons after being included in the study;
5. Patients with other non-tumor conditions that prevent them from continuing to receive this treatment plan;
6. Patients who cannot complete the study plan for various reasons after being included in the study;

# Study medication

## Overview of investigational product

In the study, study drugs are defined as Sintilimab.

|  | Sintilimab |
| --- | --- |
| Manufacturer | Innovent, China |
| Dose Form | Injection fluid |
| Strength | 100 mg |
| Route of Administration | Intravenous |

